### Target sample size

The sample size calculation is based on the primary outcome of tipping of the lower molar tooth. There are no published data on which to base the calculation, therefore local audit data were used. These data indicated that tipping of the molar (a dichotomous outcome of either less than or more than 15 degrees tipping in the vertical direction) lies somewhere between 50:50 and 60:40 for good to poor outcome in a representative group. A finding of a difference in this proportion of 10 percent between the two groups, for example proportions of 50:50 and 40:60, in the two comparison groups would be deemed to be clinically significant.

Sample size calculation for a power of 0.8 and an alpha of 0.05 indicated a sample of 124 in each group if the true population proportion is 60:40, or 171 if the proportion is 50:50. It was therefore decided to set the required sample size at 150 in each group, requiring 300 in total. Allowing for a drop-out rate of 25% our target sample size is therefore 400.

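### The stated sample sizes (124 or 171 per arm, set at 150) do not give 80% power for a 10-point difference; 150 per arm gives about 41–44%

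*Protocol article*

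**What the plan says.** All the relevant inputs are in the Target sample size section of the protocol article. The outcome is binary: tipping of the lower second permanent molar below or above 15 degrees. Local audit data suggest the split "lies somewhere between 50:50 and 60:40 for good to poor outcome in a representative group". The effect of interest is given with an example: "A finding of a difference in this proportion of 10 percent between the two groups, for example proportions of 50:50 and 40:60", which the section calls clinically significant.

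The calculation is then reported: "Sample size calculation for a power of 0.8 and an alpha of 0.05 indicated a sample of 124 in each group" for a true split of 60:40, with 171 per group for a split of 50:50. The conclusion is to "set the required sample size at 150 in each group, requiring 300 in total", and a 25% allowance for drop-out raises the target to 400. Neither the test nor its sidedness is given. The Overview under Methods/Design describes two parallel arms and a superiority framework.

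**The concern.** For proportions near one half, detecting a 10-point difference with 80% power takes well over 300 per arm. Figures of 124 and 171 are less than half of that, so they seem to belong to a larger difference than the one stated.

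The section claims 80% power for the primary comparison. If the true power is about half of that, a real 10-point effect of compensating extraction could easily give a non-significant result. The Background says that finding the procedure unnecessary would reduce the number of teeth extracted, and the dissemination section says the results will inform national guidelines. A reader who believes the power was 80% could take a non-significant result as evidence of no important difference, which the trial could not support.

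**Working it through.** **Inputs from Target sample size:** power 0.80; alpha 0.05; reference proportion p₁ of 0.50 to 0.60; difference d = 0.10; equal arms. **Assumption:** a two-sided test, because sidedness is not stated. One-sided results are also shown.

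**Required n per arm** (p̄ is the mean of p₁ and p₂):

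n = [z₁₋α/₂ √(2p̄(1−p̄)) + z₀.₈ √(p₁(1−p₁) + p₂(1−p₂))]² / d²

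- 0.50 v 0.40 (the same by symmetry for 0.60 v 0.50): [1.960 × √0.495 + 0.842 × √0.490]² / 0.01 = (1.379 + 0.589)² / 0.01 = 387.3, so **388**.
- 0.60 v 0.70: [1.960 × √0.455 + 0.842 × √0.450]² / 0.01 = (1.322 + 0.565)² / 0.01 = 355.9, so **356**.

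**Attempts to reproduce 124 and 171 with a 10-point difference:**

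| Variant | 0.50 v 0.40 | 0.60 v 0.70 |
|---|---|---|
| Two-sided, pooled | 388 | 356 |
| Two-sided, unpooled | 385 | 354 |
| Two-sided, arcsine | about 387 | about 355 |
| Two-sided, continuity-corrected | 408 | 376 |
| One-sided, pooled | 305 | 281 |

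No variant comes near 124 or 171. Other readings fail too:

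- Non-inferiority with a 10-point margin at one-sided 0.025 gives 393 (proportion 0.50) or 377 (0.60), and the trial is in any case framed as superiority.
- One-sample formulas give about 142–153 (one-sided) or 178–194 (two-sided).
- A 20-point contrast, 0.60 v 0.40, gives 97, or 107 with continuity correction.

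The nearest simple match for 171 is 0.50 v 0.65, a 15-point difference (170 per arm). From 0.60, 124 per arm corresponds to 0.60 v 0.765, a 16.5-point difference. These are back-calculations. The article does not say such contrasts were used.

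**Power for a 10-point difference:**

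Power = Φ{[d√n − z₁₋α/₂ √(2p̄(1−p̄))] / √(p₁(1−p₁) + p₂(1−p₂))}

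For n = 150 and 0.50 v 0.40: Φ[(1.225 − 1.379) / 0.700] = Φ(−0.220) = 0.413. For 0.60 v 0.70: Φ[(1.225 − 1.322) / 0.671] = Φ(−0.145) = 0.442.

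| n per arm | Two-sided power |
|---|---|
| 124 | 35–38% |
| 150 | 41–44% |
| 171 | 46–49% |
| 200 (all 400 retained) | 52–55% |

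One-sided power at 150 per arm is 54–57%.

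**Difference detectable with 80% power at 150 per arm, two-sided:** 15.9 points from 0.50; from 0.60, 15.1 points upward or 16.1 points downward.

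**Drop-out step:** 300 / 0.75 = 400, which is correct. With 388 per arm the same step gives 776 / 0.75 = 1,034.7, or 1,035 children.

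**The case against.** The strongest reply is that the 41–44% depends on a two-sided test the article never specifies. That is true. One-sided power at 150 per arm is 54–57%, and two-sided power with no drop-out at all is 52–55%. In those cases a true 10-point effect would be found slightly more often than missed. That qualifies how the consequence should be worded, but the claimed 80% is out of reach on every reading.

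It can also be said that 150 was openly chosen between two scenario figures. That is a design choice and not an arithmetic error, although 150 falls short of the article's own 171 for a split it regards as plausible. The finding does not rest on this.

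A third point is that the article cannot show whether the sample size or the target difference is the wrong entry. This stands, and it bears on the remedy: the authors must say which they intended.

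The brevity of a journal article is no defence. Difference, power, alpha and sample size are all printed in the same section and are incompatible.

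**Conclusion.** The concern holds. For the stated 10-point difference, 80% power needs 356–388 per arm two-sided, or 281–305 one-sided, against the 150 adopted. Two-sided power at 150 per arm is 41–44%, so a true 10-point effect would be missed 56–59% of the time. The design is adequately powered only for differences of about 15–16 points.

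These results assume equal arms, independent observations, reference proportions of 0.50 to 0.60 and exactly 150 evaluable children per arm. No allowance is made for clustering by site; clustering that inflates the variance of the comparison would lower power further. Because the error concerns the primary comparison's central design claim, it must be corrected.

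**What to change.** Correct the Target sample size section so that difference, power and sample size agree. The least costly version keeps recruitment as it is and states that 150 evaluable children per arm give 41–44% power (two-sided 5%) for a 10-point difference and 80% power for a difference of about 15–16 points. The figures 124 and 171 should be removed and the sidedness stated. The cost is protocol wording and a less favourable power statement.

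This discloses the shortfall without removing it. If the authors want 80% power, they must either justify a target of 15–16 points as the clinically important difference or resize to 388 per arm, about 1,035 children after 25% drop-out.

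An optional mitigation without extra recruitment is to give the tipping angle in degrees a prespecified role as the primary or key supporting analysis, adjusted for baseline factors, with the 15-degree split reported beside it. The 3D scans already yield the angle, and the statistical methods section already lists degree of tipping among its comparisons. If the angle were normal with equal spread in both arms, moving the favourable proportion by 10 points would be a shift of 0.253 to 0.271 SD. Unadjusted power at 150 per arm would then be Φ(0.253 × √75 − 1.960) = 59% to Φ(0.271 × √75 − 1.960) = 65%. The article gives no distribution for the angle, so this is an assumption, and it still falls short of 80%. The price is a less direct clinical reading than the 15-degree split. The correction to the power statement is needed whether or not this is adopted.

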### Dentist recruitment and retention strategies

Recruitment of dentists has begun and will continue to take place in the settings from which participants will be recruited:

1. Secondary care (NHS Tayside): at Dundee Dental Hospital and School, in the Orthodontic and Paediatric Department, all clinicians who see children for routine check-up appointments or non-urgent secondary care assessments, have been invited to participate in the recruitment and follow-up of children in the study. Good clinical practice (GCP) trained staff will be able to consent patients.

2. Primary care practices (including NHS Tayside practices) and orthodontic practices: in Scotland, General Dental Practitioners (GDPs) who are part of the SDPBRN Rapid Evaluation Network and dentists who have participated in other trials will be invited to participate.

It is expected that up to 40 sites will be recruited to participate in this trial. Sites will be initiated in batches of 5 to 10 sites per recruitment period. A batch of sites in an area will be started and recruitment targets reviewed before a new set of sites is initiated (See Figure 3).

**Figure 3 F3:**
[figure not shown]
Projected recruitment and study site enrollment.

To help with retaining dentists in the study, the following strategies are being employed:

1. The trial manager will maintain contact with the practitioners, manage any non-clinical queries and refer clinical problems to the dental staff.

2. Continuous Professional Development points will be made available for attendance at any meetings.

3. Newsletters will be issued during the 2 years of patient recruitment, then at 3 years and 4 years (to mark the 1 year review) and at the final 6 and 7 year time points to update dentists on trial progress and help to maintain engagement with the study.

4. A final report will be issued to all of the participating dentists.

### Participant recruitment and retention

Patients who meet the inclusion criteria will receive an invitation to take part in the trial will be identified during attendance at appointments with clinicians participating in the trial.

It is anticipated that the majority of patients will be attending for a six monthly routine check-up appointment (primary care GDP or community dentist) or a non-urgent secondary care assessment (practice-based specialist orthodontist, hospital-based orthodontic service and pediatric department).

Patients attending for routine check-up appointments or non-urgent assessments, who meet the inclusion criteria, will be assessed by the dentist for eligibility, and asked whether they wish to participate when they return for treatment at their next appointment. The patients and parents will be given information on the study to take home with them. Consent will be taken at the subsequent appointment by a dentist participating in the trial as a principal investigator (PI). Randomization will be carried out prior to this appointment and treatment.

For children who attend for urgent appointments, presenting in pain, the patients and their parents will also be approached at the time of their appointment about whether they wish to participate in the study. Because there is the need to alleviate the child’s symptoms as soon as possible, usually involving extraction of the tooth, there is no scope for 24 hours to reflect on the trial information. For this reason some patients will be invited to participate at their assessment appointment. Consent and randomization will still follow best practice, and parents and patients will still be given time to look at the patient information sheets and consider the study. The intervention in this study (extraction of a single tooth compared with extraction of two teeth) still allows the patient to return for conventional treatment (extraction of the upper FPM) should they be allocated to the intervention arm but change their mind about participation at a later date.

On enrollment to the SIXES trial, parents and patients will be given ‘calling cards’ saying that they are participating in the study, with details of their dentists and who to contact regarding the study.

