**Methods/Design:**

This is a multicenter, two-arm parallel group randomized clinical trial. Allocation will be web-based randomization. Practitioners in primary and secondary care settings, reflecting the points of presentation and treatment of eligible patients, will recruit 400 children, aged 7 to 11 years requiring extraction of lower first permanent molars but who have upper first permanent molars of good prognosis. Baseline measures (prior to treatment) and outcome data (at one and five years, or when the patient reaches 14 years of age) will be assessed through study models and child/parent questionnaires.

The primary outcome measure is degree of tipping of the lower second permanent molar, (favorable outcome is tipping less than 15°).

The secondary outcomes are type of anesthetic/sedation used, residual spacing (between lower second premolar and second permanent molar), orthodontic treatment requirement, quality of life, and over-eruption in the intervention group. Assessors will be blinded where possible.

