### Participant timeline

Patients will be identified by clinicians participating in the trial from either the patients’ own dentist or orthodontist; or a secondary care orthodontic or pediatric department.

Patients who are found, during routine dental examination or assessment, to require extraction of a lower FPM will be assessed by their dentist or orthodontist for meeting the inclusion criteria. Patients who meet the inclusion criteria will have the study discussed with them and their parents/guardians by their clinician. A participant information leaflet will be given. Patients will be given a further appointment for the extractions, at least 24 hours after receiving the information and at this time, the study will be discussed again. However if treatment is to be carried out at the same appointment (for example, where patients are in pain), there will be time allowed for the patient and parent/carer to read the documentation and ask any questions to ensure they have sufficient time and information for consent to be informed. Consent/assent processes will be carried out and then randomization undertaken. Extraction(s) will be carried out as per randomization and the remaining treatment plan.

The patient will complete the first questionnaire and have upper and lower impressions taken for study models to be cast. When the patient returns for 1-year follow-up, they will complete the Year 1 Follow-up Questionnaire and have upper and lower impressions taken for study models to be cast. When the patient returns for final follow-up (at five years or when the patient has reached 14 years of age), they will complete the Final Follow-up Questionnaire and have upper and lower impressions taken for study models to be cast.

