#### Consent and assent

Where patients attend their own primary care dentist, these dentists will act as principal investigators and will obtain consent from the patients. Patients attending the Dundee Dental Hospital and receiving treatment there will give consent to one of the trial team wherever possible. If this is not possible, a suitably trained dentist will obtain consent. Regardless of location, consent of the patients will be performed by dentists who will be conversant with the study design and protocol, and be GCP trained in line with the Research Governance Framework (RGF).

The parent(s)/legal guardian(s) of all children in the study will provide written informed consent before any study procedures are carried out and a participant information sheet will be provided to facilitate this process. Where possible, and with the agreement of the parent(s)/legal guardian(s), participating children will also be asked to provide written or oral assent. Those not competent in English will be invited to bring an interpreter with them to the subsequent treatment appointment or to request an NHS interpreter, where this service is available.

As part of the consent process parent(s)/legal guardian(s) must agree to researchers and regulatory representatives having access to their medical records for monitoring and audit purposes. Parent(s)/legal guardian(s) may withdraw their consent to participate at any time during the study.

The investigator or delegated member of the trial team and the child should sign and date the Assent form whereas the parent and investigator should sign the Informed Consent form(s) to confirm that consent has been obtained. The participant should then receive a copy of this document and a copy should be filed in the investigator site file (ISF).

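### For routine patients one sentence puts randomization before the consent appointment, contradicting the consent-first order given elsewhere; if followed, entry could depend on the allocated arm

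*Protocol article*

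**What the plan says.** *Participant recruitment and retention* describes the usual route into the trial: "It is anticipated that the majority of patients will be attending for a six monthly routine check-up appointment" or a non-urgent secondary care assessment. These families take the study information home and are "asked whether they wish to participate when they return for treatment at their next appointment". The next steps are given in two consecutive sentences. The first is "Consent will be taken at the subsequent appointment by a dentist participating in the trial as a principal investigator (PI"). The second is "Randomization will be carried out prior to this appointment and treatment".

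Other sections give the opposite order:

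- *Participant timeline*: after the study is discussed again at the extraction appointment, "Consent/assent processes will be carried out and then randomization undertaken", and extraction follows.
- *Consent and assent*: parents or guardians of all children "will provide written informed consent before any study procedures are carried out".
- Table 1 (*Data collection*): consent/assent forms and web randomization both fall in the baseline column, with consent listed first.

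*Blinding* states that staff, children and carers cannot be blinded once the group has been allocated. *Participant allocation* describes a central, web-based system.

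**The concern.** The instructions for the main recruitment route cannot all be followed. A site that works from the recruitment section would run the randomization before the visit at which the family decides. There is a practical reason why a site might do so. The abstract and the introduction both say that the number of teeth to be extracted bears on whether local anesthesia, sedation or general anesthesia is used, so knowing the arm beforehand would help in booking the appointment. With up to 40 sites planned, different sites could adopt different orders.

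Two things are at stake. The first is consent itself, since a child would be allocated within the trial before anyone had agreed to it. The second is the comparison between arms. The arms differ in whether an upper molar of good prognosis is also removed, and it is plausible that willingness to take part depends on that. If the arm is known when the family decides, entry could be selective. A central system protects the sequence up to the moment of allocation but does not protect a decision made afterwards. *Withdrawal procedures* keeps children in follow-up and analysis when their treatment changes after they have entered the study. It cannot cover a child who was randomized but never consented, because there is no permission to collect that child's data. An analysis by allocated arm would lose such children, and no later statistical method could reliably recover them.

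**Working it through.** The point rests on the order of events in the text. The protocol states no figure that needs reproducing.

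**Step 1: the order in each place.**

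| Place in the protocol article | Order given |
|---|---|
| *Participant recruitment and retention*, routine route | Randomization, then the appointment with consent and treatment |
| *Participant timeline* | Consent/assent, then randomization, then extraction |
| *Consent and assent* | Written consent before any study procedure |
| Table 1 | Same visit, consent row above randomization row |
| *Participant recruitment and retention*, urgent route | Best practice to be followed; no order spelled out |

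**Step 2: can the sentence be read another way?** The phrase about the appointment could be taken to mean only the extraction. That does not fit. The sentence just before it identifies the appointment as the one where consent is taken, and treatment is named as a separate item. No earlier agreement to take part is described on this route. The literal reading is therefore randomization before consent.

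**Step 3: does the arm become known?** The text does not say that the arm is disclosed before consent. It follows as a possibility from three facts: allocation precedes the consent visit, blinding is ruled out once the arm is allocated, and no section holds the result back until the form is signed.

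**Step 4: how large could the distortion be?** The protocol gives no decline rates and nothing on the outcome of decliners, so these are assumptions. Let *p* be the favorable rate among all allocated children, *d* the fraction of one arm that declines after learning the arm, and *r* the favorable rate those decliners would have had. The favorable rate among entrants in that arm is

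(p − d·r) / (1 − d), so the distortion is d·(r − p) / (1 − d).

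Take no true effect, *p* = 0.50 (within the range quoted from local audit in *Target sample size*) and *r* = 0.70 (assumed), with decliners in one arm only:

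- d = 5%: (0.50 − 0.035)/0.95 = 0.4895, a difference of 1.1 points
- d = 10%: (0.50 − 0.07)/0.90 = 0.4778, a difference of 2.2 points
- d = 20%: (0.50 − 0.14)/0.80 = 0.4500, a difference of 5.0 points

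With decliners in both arms, 15% in the two-extraction arm and 5% in the other, the entrants' rates are (0.50 − 0.105)/0.85 = 46.5% and (0.50 − 0.035)/0.95 = 48.9%, a difference of 2.5 points.

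If *r* = *p*, the distortion is zero for every *d*. If *r* is below *p*, its sign reverses. For comparison, *Target sample size* treats a 10-point difference as clinically significant.

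**The case against.** The best defense is that one stray sentence stands against three other places that put consent first. The remark that urgent cases will still follow best practice suggests that the authors assumed the routine route does so too. On this view the trial has an internal contradiction and has not adopted randomization before consent as its design. That is fair, and it is how the point is put here. It does not remove the problem, because the stray sentence sits in the section that describes how most children are recruited.

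Three stronger readings are tempting, and the documents do not support them.

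- A reader might infer that allocation concealment is lost and that non-entry will differ by arm. Both are conditional. Sites would have to follow this sentence over the others, and the arm would have to become known before the form is signed. Randomization is central, and no section says when the result is released.
- A reader might infer from *Participant timeline* that baseline data are collected after extraction, because "The patient will complete the first questionnaire and have upper and lower impressions taken for study models to be cast" comes after the account of extraction. That sentence opens a new paragraph which lists assessments visit by visit, with no word linking it to what came before. The abstract has "Baseline measures (prior to treatment) and outcome data", which answers the inference.
- A reader might take 2.5 points as the expected bias. The arithmetic is right, but every decline input is assumed. No section links reluctance to lose an upper tooth with later tipping of the lower second molar.

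**Conclusion.** The contradiction is real and should be corrected. On the route expected to supply most of the sample, one sentence puts randomization before consent, against *Participant timeline*, *Consent and assent* and Table 1. If that sentence is followed, children are allocated without consent, and dentists and families could decide on entry knowing the arm. Non-entry could then be selective, in a way that an intention-to-treat analysis could not repair.

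Neither the size nor the direction of any bias can be derived from the documents. About 1 to 5 points is an illustration. It rests on 5% to 20% of one arm declining, a 70% favorable rate in decliners and 50% overall, and it falls to zero if decliners resemble the rest. The finding does not depend on these numbers. It is limited to the routine and non-urgent route, because the recruitment section does not put randomization first for urgent patients.

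**What to change.** Delete or correct the sentence in *Participant recruitment and retention* so that the order is the same on every route: eligibility confirmed, written consent/assent complete, web randomization run, extraction carried out. If the arm has to be known early in order to plan the appointment, take consent earlier as well, so that randomization never precedes it. This also avoids the question of how to count children who are randomized but never consented.

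As a clarification only, state that the baseline questionnaires and impressions are completed before randomization. This agrees with the abstract's statement that baseline measures precede treatment, and it keeps the baseline quality-of-life scores free of any knowledge of the arm.

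The cost is a wording change and a line in site training. At most, some consent and baseline forms are completed at an earlier visit.
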